## 2.8. Description of the methods of data collection, instruments

As can be seen from the previous section, both self-assessment and external assessment procedures are integrated into the data collection. In both cases, psychometrically tested clinical interviews and scales are used. The collected characteristics of the efficacy study are divided into primary and secondary outcomes and include anxiety expression as well as additional psychopathological characteristics.

Personal and socio-demographic data:

- Name, place of residence, e-mail address, telephone number; age, gender, marital status, education, nationality.

Screening and diagnostics:

- MiniDIPS: (current and lifetime) diagnoses of mental disorders
- PSS-K: Personality Disorder Screening Short Form
- SCID PD: Structured Clinical Interview-Personality Disorders (for indications according to PSS-K).
- Other clinical data: psychometric data from clinical procedures, psychiatric treatment, use of psychotropic drugs, past psychotherapy/s (number, type).

Primary Outcomes:

1. Anxiety Symptomatology:

|                                             |                     |
|---------------------------------------------|---------------------|
| Self-assessment                             | BAI, PAS; GAD-7, FQ |
| External assessment                         | PAS, HAMA           |
| 2. positive outcome                         |                     |
| Positive Psychotherapy                      | PPTI                |
| Inventory Flourishing Scale                 | FS                  |
| Satisfaction with Life-Scale                | SWLS                |
| Secondary Outcome:                          |                     |
| ICD-10 Symptom Rating                       | ISR                 |
| Patient Health                              |                     |
| onnairePHQ-9                                | Questi              |
| Process Study:                              |                     |
| Hourly assessment questionnaire me patients |                     |

STU-P Interession questionnaire ISF

## 2.9. Description of the sample (participants)

The sample size was calculated using a power analysis (G\*Power). This amounts to 165 subjects; accordingly, 55 subjects would be included in each of the three intervention groups. Regardless, the following inclusion and exclusion criteria are set for the study:

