### 3. project participants

#### 3a. Recruitment and exclusion

##### 3.1. Planned number of participants

According to Power calculation at least N=165 participants (see above)

3.2. Expected duration of participation in the planned project for individual participants (duration of the study dates; period)

24-26 weeks total: Intervention: 12 weeks, each with one 90- to 100-minute session and about 45 minutes of home exercises per week; follow-up another 12 weeks.

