3.3. Characterization of participants

Minimum age: 18 Maximum age : 65

not personally capable of giving consent includable?

Yes No

Includable are

male and/or

female participants

3.4. Description of recruitment process (include all materials intended for use, e.g., advertisements):

Newspaper advertisements (have not yet been created), advertisements in online forums, internal university mailings, contacts to psychiatrists and psychotherapists, contacts to self-help groups, Facebook groups, Psychologie heute (Psychology Today).

3.5. Briefly describe the selection of participants and inclusion/exclusion criteria (sampling method, rationale, caseload estimate) (explicit rationale for inclusion of persons from protected groups, e.g., minors, temporarily or permanently incapacitated persons; if applicable).

Sample size as presented above, calculated using power analysis (G\*Power) criteria;  $p < .05$ ; 1-beta = .80; ES (between):  $d = 0.15 - 0.30$ ; 3 groups, 3 MZP. Required N=165 subjects, 55 per group.

Sample extraction: ad hoc/general sample; no other drawing is possible in this context.

Inclusion of protected groups not provided.

Inclusion criteria:

-age: 18 to 65

-Diagnosis of one of the following anxiety disorders: F40.1: Social anxiety disorder/social phobia; F41.0 Panic disorder with or without agoraphobia, F41.1 Generalized anxiety disorder.

-sufficient knowledge of German

-Average intellectual capacity (assessment during telephonic/video screening).

-Sufficient time for the weekly sessions and homework assignments.

-Acceptance of the study protocol

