3.16. Are voices, sound, images or videos recorded?

☐ Ja      No

If yes: Consent of participants to be recorded? Yes

3.17. What are you doing to ensure that the participants from the study are able to opt out or withdraw their own data?

Already in the run-up and in connection with the recruitment, the participants are informed that they can withdraw or terminate their participation in the study at any time by means of a letter (e-mail) to the study management. This will exclude them from the study with immediate effect. At the beginning of the study, the participants will be given a

consent form is submitted or sent by e-mail (see appendix), in which this procedure and all other information about the study are described. If the withdrawal is associated with a request for deletion of the individual data, the individual code must be disclosed to the study management when communicating (e-mail).

3.18. How will the data be stored and/or destroyed after the project is completed?

The data are stored electronically and kept in an encrypted order of a password-protected laptop in pseudonymous form. The data are stored for 30 years. The data will be fully anonymized and used for further research. In the consent form, the participants are informed about the data processing and agree to it with their signature.

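### The 165 required for 80% power is also the inclusion target with no allowance for loss, so the stated power holds only if nobody is lost before the time point compared

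*Protocol*

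**What the plan says.** - Section 3.5 lists the G*Power inputs: significance level .05, power .80, a between-group effect given as the range d = 0.15 to 0.30, three groups and three time points. The result is "Required N=165 subjects, 55 per group".
- Section 2.9 turns that result into the inclusion target: "This amounts to 165 subjects; accordingly, 55 subjects would be included in each of the three intervention groups".
- Section 3.1 repeats it as a floor: "According to Power calculation at least N=165 participants (see above".
- Section 3.2 gives the length of participation: "24-26 weeks total: Intervention: 12 weeks, each with one 90- to 100-minute session", plus weekly home exercises and a further 12 weeks to follow-up.
- Section 3.17 says participants are told that "they can withdraw or terminate their participation in the study at any time", and adds: "This will exclude them from the study with immediate effect". Deletion of data is a separate request.
- Section 2.7 places allocation before the T1 questionnaires and collects the T2 and T3 self-reports through a link sent to participants.
- Section 2.11 plans an intention-to-treat analysis of change from T1 to T2 and T3 with mixed linear models.

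No section gives an expected loss, an inflation of the sample or a replacement rule.

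**The concern.** The number that has to be analysed to reach 80% and the number that has to be enrolled are the same. Among the printed inputs nothing stands for loss, while the design itself provides for people leaving. A trial that enrols 165 complies fully with the protocol, yet it has the stated power only if it keeps everyone up to the time point being compared.

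The power figure is what a non-significant between-group result will be read against. If the power achieved is several points lower, such a result will be given more weight than it deserves.

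**Working it through.** **Step 1. Reproduce 165.** Section 3.5 names neither the test nor the correlation between time points, and gives a range for the effect, so reproduction needs assumptions. The between-factor test of a repeated-measures ANOVA has noncentrality

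λ = f² · N · m / (1 + (m − 1)ρ), with k − 1 and N − k degrees of freedom.

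With k = 3, m = 3, α = .05 (protocol), and f = 0.20 and ρ = 0.5 (assumed):

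- N = 165: λ = 0.04 × 165 × 3 / 2 = 9.90, power 0.804.
- N = 162: λ = 9.72, power 0.796.

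So 165 is the smallest balanced total reaching 80%, and no loss term is needed to obtain it. Other settings return 165 too (for example the within-factor test at f = 0.10, ρ = 0.5), so this shows only that 165 is consistent with zero loss. It does not identify what was computed.

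**Step 2. Lost participants contribute nothing.** Same test, with N = 165 × (1 − loss). The loss rates are assumptions.

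| Loss | N analysed | Power |
|---|---|---|
| 0% | 165 | 0.804 |
| 10% | 148.5 | 0.757 |
| 20% | 132 | 0.702 |
| 30% | 115.5 | 0.638 |

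The choice of test matters little. Each variant tried (one-way, between, within, interaction, pairwise), set to 80% at 165, gives 0.75-0.76, 0.69-0.71 and 0.62-0.65 at these three loss rates.

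**Step 3. The planned mixed model, which keeps partial data.** Take a two-arm contrast in change from T1, 55 allocated per arm, with equal correlation ρ between time points and 80% power when nobody is lost. Let l be the proportion lost in each arm. The variance of the contrast is multiplied by

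- both T2 and T3 lost, T1 kept: R = 1 + ((1 + ρ)/2) · l/(1 − l)
- T3 only lost, for the T3 contrast: R = 1 + ((1 + 2ρ)/(2 + 2ρ)) · l/(1 − l)
- T3 only lost, for the T2 contrast: R = 1

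Power = Φ(2.802/√R − 1.960), where 2.802 = 1.960 + 0.842.

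Example with ρ = 0.5 and 20% losing both: R = 1 + 0.75 × 0.25 = 1.1875, √R = 1.090, and Φ(2.571 − 1.960) = Φ(0.611) = 0.729.

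| Assumed loss | Both lost, T2 or T3 contrast (ρ = 0.5 / 0.7) | T3 only lost, T3 contrast (ρ = 0.5 / 0.7) | T3 only lost, T2 contrast |
|---|---|---|---|
| 10% | 0.768 / 0.764 | 0.771 / 0.770 | 0.80 |
| 20% | 0.729 / 0.720 | 0.737 / 0.733 | 0.80 |
| 30% | 0.683 / 0.670 | 0.695 / 0.690 | 0.80 |

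Keeping T1 data recovers about 1 to 4 points compared with step 2, but not the whole shortfall. Because allocation comes before the T1 questionnaires, a participant lost before T1 would bring nothing, as in step 2.

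**The case against.** Five points count against a stronger version.

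1. *The target is a minimum.* Section 3.1 allows more than 165, so it would be wrong to say that enrolment is capped there. But none of the sections plans over-enrolment, and exactly 165 meets the protocol.
2. *The mixed model uses partial data.* A reader might infer that 80% requires all 165 to provide both T2 and T3. It does not: loss at T3 alone leaves the T2 comparisons untouched. The complete-loss figures of step 2 are also too pessimistic for participants who did provide T1. What stands is that loss before T2 still costs power under the model.
3. *No loss rate is given.* One might say that the trial fails at ordinary loss. The protocol supplies no rate to call ordinary. The percentages here are assumptions, and the withdrawal text in section 3.17 shows that loss is foreseen, not how much. Nor does it say that data already collected are removed, since deletion needs a separate request.
4. *The three-month hypotheses.* A reader might extend the shortfall to effectiveness hypotheses 12 to 16. Numbers 12 to 15 concern stability within one arm and 16 is exploratory, while the 80% in section 3.5 is attached to a between-group effect. No power was claimed for them, so no shortfall from a claim can be shown. The T3 figures above apply to between-arm comparisons at T3.
5. *The effect is not identified.* This is the strongest objection. At f = 0.20, moving ρ from 0.3 to 0.7 moves power at 165 from 0.89 to 0.72, as much as the loss does. If the printed range is f (ρ = 0.5), power at 165 runs from 0.54 at 0.15 to 0.99 at 0.30, and at 0.30 it is still about 0.95 with 30% loss. If it is d, a pairwise comparison at 55 per arm has only about 12% to 35% power before any loss. The loss calculation is therefore conditional on the effect at which 165 gives the claimed 80%. That limits the claim but does not remove it, because the protocol ties .80 to 165.

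**Conclusion.** The point holds in a limited form. The required number and the inclusion target coincide, no loss allowance is made, and the stated 80% is reached only without loss before the time point compared. Under the planned model, assumed loss of both T2 and T3 in 10%, 20% or 30% costs about 3-4, 7-8 or 12-13 points. Loss of T3 alone costs about 3, 6-7 or 10-11 points at T3 and nothing at T2. These sizes rest on the assumed loss rates, equal loss across arms, equal correlations of 0.5 to 0.7, T1 observed for everyone, and an effect for which 165 gives exactly 80%.

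The multiplication 3 × 55 = 165 is correct. What is wrong is attaching 80% to 165 enrolled. It should be corrected, but it does not undermine the design.

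**What to change.** In sections 2.9, 3.1 and 3.5:

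- State the expected proportions of allocated participants who will provide T2 and T3, with their basis.
- Replace 80% for 165 enrolled with the power, or the detectable effect, at those numbers under the mixed model of section 2.11, separately for T2 and T3 comparisons.
- Base that figure on one effect size with its metric, the test and the correlation assumed. The range d = 0.15 to 0.30 does not show which effect 165 was computed for, and a loss-adjusted figure cannot be stated without it.

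The cost is a few sentences and one recalculation, and the stated power may be less favourable. Enrolling more is not required. If the team prefers to keep 165 with complete data, the enrolment is 165/(1 − loss): 184 at 10% (186 if balanced), 207 at 20% and 236 at 30% (237 if balanced), again with assumed rates.

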### Inclusion criteria:

- Age from 18 to 65
- Diagnosis of any of the following anxiety disorders: F40.1: Social anxiety disorder/social phobia; F41.0 Panic disorder with or without agoraphobia, F41.1 Generalized anxiety disorder.
- sufficient knowledge of German
- average intellectual ability (assessment during telephone/video-based screening)
- Sufficient time for the weekly sessions and homework assignments
- Acceptance of the study protocol

### Exclusion Criteria:

- Participation in psychotherapeutic and/or psychological treatment or counseling planned at the same time or in the following three months, as well as participation in other psychological group offers
- Symptoms of major depression, bipolar affective disorder, or mania (current as well as history), psychotic, schizophrenic, and/

- or schizoaffective disorder, acute grief reaction, severe anorexia or bulimia, substance dependencies (alcohol, illicit drugs)
- severe personality disorders, especially borderline, narcissistic, anti/dissocial and paranoid personality disorder
- acute suicidality
- Switch, dose change, or complete discontinuation of psychotropic drugs in the past or following three months
- Lack of decision-making capacity.

#### 2.10. Description of the survey locations

The screening as well as the intervention and the surveys take place in an online format. However, for the implementation of the online interventions, fixed locations are determined for the psychologists. In Salzburg, the online interventions are conducted on the premises of the Counseling Center for Clinical Psychology, Psychotherapy & Health Psychology.

#### 2.11. Description of the method of data analysis

SPSS: Changes from time point 1 to time point 2 and time point 3 are calculated using an ITT with hierarchical mixed linear models.

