"Therapy Tool for Anxiety Disorders" by Hagena and Gebauer (2014). The treatment manual of the control group is thematically based on that of Positive Psychotherapy, but strongly shortened. The treatment manuals of PPT and KVT each comprise 12 group sessions of 90-100 minutes each and one individual session. The treatment manual of the control group comprises 12 sessions, three of which (the first, the sixth and the twelfth) take place in an online group setting, and the remaining nine are self-completed with the help of instructional videos and e-mail communication. All therapy sessions take place online. The individual groups consist of six to eight participants. The participants in each group also have access to a website created specifically for the study. This website provides work materials, audio files and instructional videos. In addition, it offers the possibility of contacting the study director via a chat function; it also serves as a virtual bulletin board to make certain exercises visible in anonymized form. The study includes three measurement time points, a pre- and post-measurement and a follow-up after three months. The treatments are carried out by psychologists in training as clinical psychologists and psychological psychotherapists in Austria and Germany. All psychologists are intensively trained in the respective manuals, participate in regular intervision sessions and receive supervision from experienced representatives of Positive Psychology and Cognitive Behavioral Therapy at regular intervals. All group sessions are recorded and discussed in the supervision. Each session is checked for adherence to the manual. As mentioned above, the study also includes a process efficacy study. In this study the intra-session processes as well as the inter-session processes of the therapy with Positive Psychotherapy and Cognitive Behavioral Therapy will be evaluated and related to the therapy outcome. Intra-session processes are understood as all those changes that occur directly in response to specific events in the therapy session, whereas inter-session processes are defined as processes of change between two sessions that are brought about by memories and representations of the session (Orlinsky & Geller, 1993). Intra-session processes will be assessed with the help of the Berner Stundenbeurteilungsbogen für Patienten (Flückiger et al., 2010), where patients will be asked after each session whether they have experienced it and whether they think it has brought progress, on the one hand in the sense of the

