## 2.6. Research Design

3x3 variance-analytic within-subjects design (within-subjects: repeated measures factor with three measurement time points: Pre, Post, Follow-up after three months). Between Subjects: Three treatment groups: two online.

conducted intervention and a low-level guided comparison group Controlled intervention study based on written treatment manuals; explicit inclusion and exclusion criteria (see below); rational sample design (see below); randomized patient assignment => RCT.

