5. The 12-week intervention based on the two manuals is conducted by psychologists in training as clinical psychologists or psychological psychotherapists in a dual trainer setting (two therapists). All therapists are intensively trained in

The group members are trained in the respective manuals, regularly update their work, and also receive regular supervision from experienced representatives of Positive Psychology and Cognitive Behavioral Theory. All group sessions are recorded and discussed in the supervision. Each session is evaluated for its adherence to the manual.

6. Before each therapy session, participants complete the Intersession Questionnaire (ISF) online for process analysis of the therapies, and after each session they complete the Patient Hourly Evaluation Form (STU-P) online.

7. The second questionnaire survey (T2) takes place after the last therapy session. For this purpose, the participants are sent the link to the online survey again. The same self-assessment procedures are used as for T1. This time, too, there will be an external assessment. This is done by the therapists using the Panic and Agoraphobia Scale (PAS) and the Hamilton Anxiety Scale (HAMA).

8. Three months after the end of the online groups, the participants receive another email with a link and a request to complete the questionnaire battery (=Follow-Up, T3). This time, too, the same self-assessment procedures are given as in T1 and T2. At this point of measurement, no further external assessment takes place.

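### Treatment is given in therapy groups, but neither the stated design, the analysis sentence nor the sample size of 165 names a therapy-group level

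*Protocol*

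**What the plan says.** Analysis (Protocol 2.11), in full apart from naming the software: "Changes from time point 1 to time point 2 and time point 3 are calculated using an ITT with hierarchical mixed linear models". No level, random effect or covariate is named.

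Design (Protocol 2.6): "3x3 variance-analytic within-subjects design". The within factor is a "repeated measures factor with three measurement time points", and the other factor is given as "Between Subjects: Three treatment groups". No therapy-group factor is listed.

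Delivery (Protocol 2.3): "The individual groups consist of six to eight participants". The PPT and KVT manuals "each comprise 12 group sessions of 90-100 minutes each and one individual session". The comparison programme also has 12 sessions, "three of which (the first, the sixth and the twelfth) take place in an online group setting"; the other nine are worked through alone. Section 2.7, step 5, says that the intervention under the two manuals is led "in a dual trainer setting (two therapists").

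Sample size (Protocol 2.9 and 3.5): 165 participants, 55 per arm, from G*Power with alpha 0.05, power 0.80, a between-group effect of d = 0.15 to 0.30, three groups and three measurement points. No ICC or design effect is among the inputs.

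Baseline (Protocol 2.7): GAD-7, BAI, FQ and PAS are taken at online pre-screening. The T1 questionnaires are completed after random allocation.

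**The concern.** Participants are allocated individually and then share sessions and therapists with five to seven others. Their outcomes can become correlated through the group, and the protocol's process study itself supposes that what happens in sessions drives outcome. If the analysis leaves this out, every participant counts as an independent observation. Standard errors are then too small, tests reject too often and confidence intervals are too narrow. This matters for the superiority hypotheses. It also matters for hypothesis 5, a comparable decrease under PPT and KVT, because an interval that is too narrow overstates the evidence for comparability. That contrast lies between the two arms delivered wholly in groups.

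The planned power has the same weakness: without a cluster term, 165 gives 80% only for independent participants.

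A smaller matter is how baseline enters. Section 2.11 speaks of changes from T1 and names no covariate. A plain change score estimates between-arm contrasts less precisely than a baseline-adjusted analysis.

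**Working it through.** **Inputs from the protocol.** N = 165, 55 per arm (2.9, 3.5); group size m = 6 to 8 (2.3); alpha 0.05 and power 0.80 (3.5); three arms and three occasions (2.6, 3.5).

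**Assumptions.** The ICC is taken as 0.01, 0.05 and 0.10. The correlation between occasions, rho, is 0.5 for power and 0.3 to 0.8 for the baseline comparison. The protocol gives neither.

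**1. Groups per arm.** 55/8 = 6.9 and 55/6 = 9.2, so about 7 to 9.

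**2. The planned figure.** For the between-factor test of a repeated-measures ANOVA on independent participants, the noncentrality is λ = f²·N·3/(1 + 2·rho), with 2 and N − 3 degrees of freedom. With f = 0.20 and rho = 0.5, λ = 0.04 × 165 × 3/2 = 9.9 and power is 0.804. At N = 162 power is 0.796, so 165 is the smallest balanced total. This reproduces the stated size without a group term, but f = 0.20 and rho = 0.5 are not in the protocol. The value 0.20 lies inside the printed range only if d is read as Cohen's f.

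**3. Effect of omitting the group level when both arms are clustered (PPT against KVT).** The design effect is DE = 1 + (m − 1)·ICC. The true standard error is √DE times the reported one. The true two-sided level is 2·[1 − Φ(1.96/√DE)].

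| ICC | DE (m = 6 to 8) | √DE | True level |
|---|---|---|---|
| 0.01 | 1.05–1.07 | 1.02–1.03 | 0.056–0.058 |
| 0.05 | 1.25–1.35 | 1.12–1.16 | 0.080–0.092 |
| 0.10 | 1.50–1.70 | 1.22–1.30 | 0.110–0.133 |

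For m = 7 and ICC 0.05: DE = 1 + 6 × 0.05 = 1.30, √DE = 1.14, 1.96/1.14 = 1.72, true level 0.086. A simulation of 20,000 trials with 8 groups of 7 per arm gave 0.083 for the ordinary t-test and 0.048 for a t-test on group means. At ICC 0.10 the two figures were 0.125 and 0.050.

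**4. Contrasts with the comparison arm.** As a lower bound, treat that arm as unclustered. The standard-error ratio is √[(DE + 1)/2], which gives 1.01–1.02, 1.06–1.08 and 1.12–1.16 at the three ICCs. The true level is 2·[1 − Φ(1.96/ratio)] = 0.053–0.054, 0.065–0.071 and 0.080–0.092.

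**5. Power and size, clustering in all arms.** Replace N by 165/DE in step 2, or inflate N to 165 × DE.

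| ICC | Power at N = 165 | Power with group-based df | Total N for the planned power |
|---|---|---|---|
| 0.01 | 0.774–0.782 | 0.706–0.735 | 174–177 |
| 0.05 | 0.665–0.702 | 0.599–0.654 | 207–223 |
| 0.10 | 0.556–0.615 | 0.497–0.570 | 248–281 |

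The third column uses denominator degrees of freedom of groups minus 3, with 27, 24 and 21 groups in all for m = 6, 7 and 8. With weaker clustering in the comparison arm the losses are smaller.

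**6. Baseline, between-arm contrasts only.** With unit variance, a change score has variance 2(1 − rho) and a baseline-adjusted analysis 1 − rho². The ratio is (1 + rho)/2: 0.65 at rho = 0.3, 0.75 at 0.5, 0.85 at 0.7 and 0.90 at 0.8. Adjustment therefore cuts variance by 10% to 35%.

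**The case against.** The best defence is that section 2.11 is silent, not wrong. A hierarchical model may mean occasions within participants, or participants within therapy groups as well, and a protocol often leaves the levels to the analysis plan. This stands. A reader might infer that the planned analysis definitely has no group level and that its standard errors are therefore too small. The text does not support that; it supports only that no group level is named.

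Three further stronger readings also fail.

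- *That every arm contrast suffers equally.* The comparison arm meets as a group in 3 of 12 sessions, and the therapist pair is described for the two manuals. Only PPT against KVT compares two fully group-delivered arms. The protocol also does not say that groups are closed to later entrants.
- *That 2.6 prescribes an ANOVA in conflict with 2.11.* Section 2.6 is headed as design and can be read as a factor layout; 2.11 is the section on method.
- *That analysing change from T1 is an error, or throws away free precision.* Several hypotheses are pre-post changes within an arm, so change is a stated target, and a mixed model with a common baseline mean also estimates change without that loss. T1 follows allocation, so adjusting for it can carry a reaction to the allocation if participants know it by then.

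Deferral to an analysis plan does not answer two parts. The sample size is fixed in this protocol without a cluster term. Group membership must also be captured prospectively: the data list in 2.8 names no group identifier, research data are held under self-generated codes (3.10), and the study director cannot link names to those codes (3.11). Without a group ID, a later plan may be unable to fit the model.

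**Conclusion.** The point holds in conditional form. Delivery in groups of six to eight creates a possible source of correlation that the stated factors, the analysis sentence and the power inputs all leave unnamed. If the model is fitted on time and treatment alone and the ICC is above 0, tests are too liberal. At an assumed ICC of 0.05 the true level is about 0.080–0.092 for PPT against KVT, and as low as 0.065–0.071 for contrasts with the comparison arm if that arm is unclustered. At ICC 0.01 the effect is slight.

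Even with a correct model, power at 165 would fall from 0.80 to about 0.67–0.70 at ICC 0.05 with clustering in all arms, and to 0.60–0.65 with group-based degrees of freedom. These power figures rest on the assumed f = 0.20 and rho = 0.5 that reproduce 165. The baseline matter is secondary: it concerns precision of between-arm contrasts and no bias is shown.

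**What to change.** 1. In 2.11, specify occasion within participant within therapy group, with a random therapy-group effect whose variance may differ by arm, and Satterthwaite or Kenward-Roger degrees of freedom. If T1 stays in the outcome vector, let the group effect act on T2 and T3: a group intercept constant over time cancels from the change and would leave the problem in place.
2. Record a therapy-group ID with the pseudonymised questionnaire data from the first group onward.
3. In 2.9 and 3.5, state that 165 assumes no clustering, and give power over a range of ICCs.
4. Secondary, for between-arm contrasts: adjust for the pre-allocation screening score where one exists (BAI, PAS, GAD-7, FQ). Use T1, as covariate or through a common baseline mean, only if it is collected before allocation.

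The cost is wording and one recorded variable. Intervals widen if the ICC is positive, by the √DE factors shown and somewhat more through the smaller degrees of freedom. Baseline adjustment may offset part of this: at m = 7, ICC 0.05 and rho 0.5 the net variance factor against an unclustered change score is 1.30 × 0.75 = 0.975, if the pre-screening score correlates with outcome as strongly as assumed.
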